### Statistical analysis

In the analysis of clinical data, an ‘intention-to-treat’ analysis will be carried out. This analysis will include elemental ‘head-to-head’ descriptions and comparisons between intervention and control groups. Specifically, descriptive statistics (mean and 95% confidence intervals for metric variables with a normal distribution; median and interquartile range for metric variables without a normal distribution; frequency distribution for categorical variables) will be defined for each variable in both groups. To check the main hypothesis all variables will be compared (t0-tk) by means of the ANOVA test with adequate post-hoc contrasts for normally distributed variables or the Kruskal-Wallis H test. Finally, different multivariate analysis including multilevel regression analysis will be included if required. Improvement effect size will be calculated as well.

In the cost-analysis, direct costs will be calculated `ing to the medication-derived costs those derived from the use of sanitary services (visits to Primary Care, Specialized services and Emergencies, as well as hospitalizations). Medical cost will be calculated by determining price per milligram (including VAT) during the study period according to the 2011 Vademecum. Total cost of pharmacological treatment will be calculated multiplying price per milligram by daily dose in milligram and length of treatment (in days). Cost derived from health services and indirect costs will be calculated.

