**Methods:**

Multicenter, randomized, controlled, two arm-parallel, clinical trial involving 300 patients over 18 years old with a diagnosis of Major Depression. Major depression will be diagnosed by means of the Mini-International Neuropsychiatric Interview. The Beck Depression Inventory total score at the end of the study will constitute the main efficacy outcome. Quality of Life and Social and Health Care Services Consumption Scales will be also administered. Patients will be assessed at three different occasions: baseline, 6-month follow-up and 12-month follow-up.

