## Methods

### Hypothesis and objectives

The first hypothesis of the present study is that patients assigned to the intervention group receiving specific hygienic-dietary recommendations will show a significantly greater improvement in clinical measures of depression in comparison to control group patients. The second hypothesis is that significant differences in health costs will be found between both groups, with patients in the intervention group showing lower expenses. Therefore, the main objective is to evaluate the effectiveness and efficiency of giving specific hygienic-dietary recommendations to depressive patients in Primary Care settings. Secondary objectives are to evaluate changes in direct and indirect costs, to specify a profile of patients who benefit from this intervention and to identify the most frequent inconveniences for patients leading to non-adherence to these recommendations.

The present study is a randomized controlled clinical trial under “real world” conditions. Patients will be allocated to one of these two conditions:

1 Treatment as usual prescribed by their GP plus specified hygienic-dietary recommendations (intervention group)

2 Treatment as usual prescribed by GP plus unspecified hygienic-dietary recommendations (control group)

The study design is shown in Table 1.

**Table 1 T1:** STUDY SCHEDULE

	***“TRIAGE”***	***BASELINE***	***SIXTH MONTH***	***TWELFTH MONTH***
**Criteria compliance evaluation**	**X**			
**Discussion of the study information leaflet**	**X**			
**Signed Consent Form**	**X**			
**MINI Interview**		**X**		
**Sociodemographic questionnaire**		**X**		
**Clinic questionnaire**		**X**	**X**	**X**

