### Sample size and randomization

Statistical analysis will be based on head-to-head comparisons between the group receiving the hygienic-dietary recommendations and the “treatment as usual” group. Based on previous research, we expect that the mean difference between both groups in the main variable (BDI Total score) will be of at least 3 points (SD=6). Assuming an alpha risk of 0.01 and two tails, with a study power of 90% the corresponding sample size is 119 patients per group. With an estimated withdrawal rate of 20%, the sample size will require approximately 150 patients in each group. Thus, the total sample size of the study will be 300 patients.

Randomization will take place for each patient once participation is agreed to and the written informed consent signed. Every GP participating in this study will be provided with identically sealed envelopes codified with a numerical code that identifies the contents. These codes will be kept by the head of the research team. Half of the envelopes will contain the specific hygienic-dietary recommendations under consideration while the other half will contain “control” unspecified hygienic-dietary recommendations. In all cases, these recommendations will be written on a sheet of paper. The GP will randomly choose an envelope and ask the patient to follow the recommendations written inside.

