### Outcomes and instruments

The main outcome in this study is symptom severity as measured by the validated Spanish version [21] of the Beck Depression Inventory (BDI-II) [22]. This is one of the most commonly used instruments to assess severity of depressive symptoms in pharmacological and psychological research. This instrument is widely used as it allows patient self-rating of depressive symptoms, avoiding evaluation bias. This is important to our study as, although they will be blinded to treatment condition, it is presumed that it will be easy for evaluators to identify which kind of recommendation each patient received during follow-up assessments. Moreover, the BDI is little influenced by somatic symptoms experienced by patients.

Other variables assessed in our study are:

– Socio-demographic variables such as gender, age, marital status, education level, occupation, economic status and hygienic-dietary habits.

– Psychiatric comorbidity will be assessed by means of the Mini International Neuropsychiatric Interview (MINI) and the State-Trait Anxiety Inventory (STAI). The MINI is a structured diagnostic psychiatric interview designed to diagnose according to DSM-IV and ICD-10 criteria [23,24]. This psychiatric interview will allow a diagnosis of Major Depressive Disorder at the baseline and also will permit the exclusion of other severe comorbid psychiatric disorders. The STAI is a self-rated inventory assessing two independent factors: State anxiety (a transitory emotional condition) and Trait anxiety (relatively stable anxious tendency). This inventory has been adapted and validated in the Spanish population [25].

– Quality of life will be measured with the EuroQol 5D (EQ-5D), which is a standardized instrument used as a measure of health outcome. The Spanish version will be administered [26].

– Health Care Services Consumption will be measured by the Spanish version of the Client Service Receipt Inventory (CSRI) [27], an instrument that allows the collection of data regarding social and sanitary services use as well as other data regarding economic impact (eg: time on sick leave) in the previous twelve months.

Assessments will take place at baseline and after 6 and 12 months.

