## Discussion

This study represents a great opportunity for the improvement with minimal costs of the effectiveness of depression treatment. Results of a preliminary study [9,13] pointed out that significant improvement of depressive symptoms can be achieved with this simple intervention. Its feasibility for the sanitary system derives from its low time consumption for health providers and the low cost of its implementation. Moreover, no significant adverse events or security problems derived from this intervention are expected.

Considering the low-restrictive nature of inclusion and exclusion criteria of the present study, problems for the recruitment of patients are not expected. The sample size will enable the determination of the profile of patients that could benefit from this simple intervention. It will also provide a better understanding of the reasons why some patients do not adhere to these recommendations, with the objective of eliminating this trend. The development of this research line in Primary Health Care settings is of great interest as well.

However, this study also has some limitations that will be taken into account. The main limitation derives from the fact that although GPs will be blinded to patient allocation, it is presumed that they will easily be able to identify which group the patient has been assigned to in the follow-up assessments. This is a potential bias as GPs could be induced to change pharmacological treatments based on this knowledge. In order to minimize this effect, we will ask participant GPs to stay as oblivious to patient allocation as possible. In case patient allocation is suspected, they will be asked to maintain a neutral attitude to patient comments regarding the recommendations they have received. Raters will also be blinded to treatment condition but, again, it will be easy for them to suspect patient allocation from the information provided by patients during the assessments. This could obviously introduce involuntary bias. To correct this possible bias, self-applied instruments will be preferred as main outcome variables.

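### The analysis section checks the main hypothesis on all variables, although the protocol names and sizes for a single outcome, BDI total score at the end of the study

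*Protocol article*

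**What the plan says.** Three places in the protocol article point to a single outcome.

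- Abstract, Methods: "The Beck Depression Inventory total score at the end of the study will constitute the main efficacy outcome".
- Outcomes and instruments: "The main outcome in this study is symptom severity as measured by the validated Spanish version" of the BDI-II. The remaining measures are then listed as other variables.
- Sample size and randomization: BDI total score is called the main variable, with an expected difference of at least 3 points and an SD of 6. "Assuming an alpha risk of 0.01 and two tails, with a study power of 90% the corresponding sample size is 119 patients per group".

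The Statistical analysis section gives the rule for testing: "To check the main hypothesis all variables will be compared (t0-tk) by means of the ANOVA test", with post-hoc contrasts, or by Kruskal-Wallis where variables are not normally distributed. This is the only sentence in the article that says how the main hypothesis is tested. It names neither the BDI nor the 12-month visit, and t0-tk is not defined. The section states no significance level.

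Hypothesis and objectives words the first hypothesis as "significantly greater improvement in clinical measures of depression in comparison to control group patients". Table 1 schedules the BDI, STAI, EQ-5D and CSRI at baseline, month 6 and month 12.

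**The concern.** This is a conflict between two statements in the article, not a detail left for an analysis plan. One set of sections commits to one variable, at one time according to the Abstract. The operative analysis sentence assigns every variable to the main hypothesis.

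If that sentence is followed, the authors could report the main hypothesis as supported by the BDI at month 6, or by an anxiety or quality-of-life score, without a difference in the outcome the trial was sized on. The 1% two-sided error used for sizing would then not be the error rate of the trial's main claim. The choice of variable or visit could also be made after seeing the data. The article itself expects allocation to be easy to guess at follow-up, which makes a fixed endpoint more valuable.

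**Working it through.** **Inputs**

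- Difference 3 points, SD 6, two-sided alpha 0.01, power 90%, withdrawal 20% (Sample size and randomization).
- Two follow-up visits, months 6 and 12 (Outcomes and instruments; Table 1).
- The STAI yields two scores, State and Trait (Outcomes and instruments).

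**1. Reproduce the sample size.**

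n per group = 2 × SD² × (z₀.₉₉₅ + z₀.₉₀)² / difference²
= 2 × 36 × (2.5758 + 1.2816)² / 9
= 8 × 14.88 = 119.04.

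The stated 119 is reproduced, with power 0.900 at 119 per group. For withdrawal, 119 / (1 − 0.20) = 148.75, so 149, which the article gives as approximately 150. The calculation is sound, and it is a calculation for one BDI comparison at 1%.

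**2. Count the tests that the analysis sentence could bring into the main hypothesis.**

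- Narrow reading, depression severity only: BDI at months 6 and 12, so 2 tests.
- Wider reading, clinical scales: BDI, STAI-State, STAI-Trait and EQ-5D, each at months 6 and 12, so 4 × 2 = 8 tests.

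Costs are left out because they have their own hypothesis and their own analysis paragraph. Physical parameters are left out because they are not measures of depression.

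**3. Chance of at least one false positive.**

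Assumptions: each test at 0.01, independent tests, and any one positive result taken as support.

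Chance = 1 − (1 − 0.01)^k

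| Reading | k | Calculation | Result |
|---|---|---|---|
| BDI at month 12 only (as sized) | 1 | 1 − 0.99 | 1.0% |
| BDI at both visits | 2 | 1 − 0.9801 | 2.0% |
| BDI, STAI-State, STAI-Trait, EQ-5D at both visits | 8 | 1 − 0.9227 | 7.7% |

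These scores are likely to be correlated within patients, which lowers the figures. In the limit of complete correlation each falls back to 1.0%. The ranges are therefore 1.0% to 2.0% and 1.0% to 7.7%.

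**4. After the change.** One test of BDI total at month 12 at two-sided 0.01 has a type I error of 1% and 90% power at 119 per group, so the total of 300 stands.

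**The case against.** The best defence is that the rest of the article already limits the main hypothesis. It concerns measures of depression, and the BDI is the only depression severity scale scheduled at follow-up. The STAI is placed under psychiatric comorbidity and the EQ-5D under quality of life. A strict reader would not accept a difference in quality of life as support. This has force, and it is why the narrow two-test reading is shown. It does not remove the conflict: the analysis sentence still says all variables, and the BDI at month 6 remains open even on the strictest reading.

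Several stronger readings are tempting, but the article does not support them.

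- *The analysis section contradicts the 0.01 level.* It states no test level, so there is nothing to contradict. Not repeating 0.01 there is the kind of detail an article may leave to a fuller document.
- *Tests will be run at 0.05, so the error is far larger.* That level appears nowhere as a test level. The 95% intervals in the section are part of the descriptive statistics.
- *Any single significant result establishes the hypothesis.* The article says only that variables will be compared. The rule in the calculation is an assumption made to bound the problem.
- *Costs, blood pressure, weight and similar measures all count toward the main claim.* The first hypothesis and the separate cost paragraph argue against this.
- *The Discussion declares several primary outcomes.* The phrase "self-applied instruments will be preferred as main outcome variables" explains a preference for self-rated over rater-scored instruments. It does not define endpoints.
- *Every visit is certain to be tested.* The notation t0-tk is undefined and may denote change from baseline. With two arms, the post-hoc contrasts would most naturally be between time points, but this is not stated.

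**Conclusion.** The point holds as a conflict over which variable and visit test the main hypothesis. The sample size is correct, and the 0.01 level is not itself contradicted.

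The size is modest on the narrow reading, up to 2.0%, and larger on the wider one, up to 7.7%, against 1% planned. Both figures rest on three assumptions: 0.01 per test, independence (an upper bound), and any one positive result being read as support. The test counts are taken from Table 1 and the outcome list; the article does not state them. The conflict itself does not depend on these figures. Because the sentence governs the confirmatory conclusion, it should be settled before outcome data are analysed.

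**What to change.** Replace the sentence in Statistical analysis with:

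> The main hypothesis is tested once, on BDI-II total score at 12 months, at two-sided alpha 0.01; BDI-II at 6 months and all other variables are secondary and do not establish the main hypothesis.

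The choice between ANOVA and Kruskal-Wallis can follow as a separate sentence, with t0-tk defined. The cost hypothesis keeps its own paragraph and is unaffected.

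The cost is wording only. Power remains 90% at 119 per group, and the total of 300 does not change.

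### The main BDI comparison is left as an unadjusted t0-tk ANOVA or Kruskal-Wallis chosen on normality; one baseline-adjusted comparison of 12-month BDI should be fixed as primary

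*Protocol article*

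**What the plan says.** - **Outcome.** The abstract's Methods paragraph states: "The Beck Depression Inventory total score at the end of the study will constitute the main efficacy outcome". The last assessment is at 12 months.
- **Sample size.** Under Sample size and randomization: "we expect that the mean difference between both groups in the main variable (BDI Total score) will be of at least 3 points (SD=6"). The error rate is set by "Assuming an alpha risk of 0.01 and two tails", and "with a study power of 90% the corresponding sample size is 119 patients per group". For losses: "With an estimated withdrawal rate of 20%, the sample size will require approximately 150 patients in each group". The section does not say whether SD 6 belongs to the final score or to the change from baseline.
- **Test.** Under Statistical analysis, the main hypothesis is checked by comparing all variables t0-tk "by means of the ANOVA test with adequate post-hoc contrasts for normally distributed variables or the Kruskal-Wallis H test". Baseline BDI is not named as a covariate. After that, "different multivariate analysis including multilevel regression analysis will be included if required".
- **Data available.** Table 1 schedules the BDI at baseline, month 6 and month 12.

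**The concern.** Three features of the stated test are badly fixed for a two-arm trial with one main outcome at one time point.

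1. **The quantity is not defined.** The term t0-tk can mean change from baseline or a comparison across visits. The abstract's outcome is the end-of-study score.
2. **The test depends on the data.** ANOVA or Kruskal-Wallis is chosen on normality, with no stated rule, and regression follows only if found necessary. With about 119 per group, a comparison of means does not need this switch. A rank test also gives no estimate of the 3-point mean difference on which the trial was sized. Post-hoc contrasts have no role in a comparison of two arms.
3. **Baseline BDI is used inefficiently.** It is measured on every patient. An unadjusted comparison of final scores ignores it, and a change score forces its coefficient to 1. Adjustment lets the data set the coefficient.

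At stake are avoidable loss of precision and a primary result open to choice after the data are seen.

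**Working it through.** **Inputs from the protocol article (Sample size and randomization):** difference 3, SD 6, two-sided alpha 0.01, power 90%, 119 per group, withdrawal 20%.

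**Assumptions, not in the document:** the correlation r between baseline and month-12 BDI (0.3 to 0.6 shown) and the baseline SD (6, then 5, 4 and 3).

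**1. The plan's own figure.** n per group = 2 × [SD × (z₀.₉₉₅ + z₀.₉₀) / difference]² = 2 × [6 × (2.5758 + 1.2816) / 3]² = 119.04. Power at 119 per group is 90.0% by the normal approximation and 89.5% by the noncentral t. Inflation: 119 / 0.80 = 148.75, so 149, or about 150. The stated figures reproduce. A two-group ANOVA is equivalent to the two-sample t-test behind this calculation, so lack of adjustment does not itself break the 90%.

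**2. SD 6 as the final-score SD, with equal SDs at baseline and month 12.**
- SD of change = 6 × √(2(1 − r))
- Residual SD after baseline adjustment = 6 × √(1 − r²)

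Power by noncentral t, 119 per group, two-sided alpha 0.01:

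| r | SD of change | Power, change score | Residual SD, adjusted | Power, adjusted |
|---|---|---|---|---|
| 0.3 | 7.10 | 74.6% | 5.72 | 92.5% |
| 0.4 | 6.57 | 82.1% | 5.50 | 94.5% |
| 0.5 | 6.00 | 89.5% | 5.20 | 96.8% |
| 0.6 | 5.37 | 95.6% | 4.80 | 98.6% |

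The two SDs show where the change score loses: 6√(2(1 − r)) exceeds 6 only when r is below 0.5. The adjusted SD never exceeds 6, and never exceeds the SD of change.

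**3. Smaller baseline SD.** Entry is limited to mild to moderate BDI scores (Study sample), which may narrow the baseline spread. With final SD 6 and baseline SD b, SD of change = √(36 + b² − 12rb). At r = 0.3:

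| b | SD of change | Power, change score |
|---|---|---|
| 6 | 7.10 | 75% |
| 5 | 6.56 | 82% |
| 4 | 6.13 | 88% |
| 3 | 5.85 | 91% |

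Adjusted power stays at 92.5% in every row, because the residual SD depends only on the final SD and r.

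**4. SD 6 as the SD of change.** The change-score test then keeps the planned power of about 90%. With equal SDs, the adjusted residual SD is 6 × √((1 + r)/2). At r = 0.5 this is 5.20, with power 96.8%.

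**5. Kruskal-Wallis between the two arms.** On normal data, with relative efficiency 0.955, the effective size is 119 × 0.955 = 113.6 per group and power is about 88.4% (normal approximation, against 90.0% for the t-test). The loss is under 2 points.

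**The case against.** The strongest reply is that nothing here is invalid. The sample size reproduces. Two-group Kruskal-Wallis is equivalent to the Wilcoxon rank-sum test and is a valid test between arms. The sentence covers all variables, so it may be generic, and t0-tk may mean a repeated-measures comparison, where post-hoc contrasts across three visits make sense. All of this stands, and it limits the point to efficiency and to fixing one analysis.

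A reader might infer four stronger things that the document does not support.

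- **That baseline BDI is discarded.** If t0-tk is a change score, baseline enters with a coefficient of 1. That is inefficient use, not omission.
- **That the trial tests something other than what it was sized on.** Under randomization, the expected between-arm difference in change equals the expected difference in final score. Both target the 3 points, and only precision differs. Change also fits the first hypothesis, which speaks of greater improvement.
- **That withdrawals are dropped.** The section declares intention-to-treat and says nothing about excluding patients without a later BDI. The 20% inflation suggests about 119 observed per group, but a missing-data rule is a detail that an article may leave to the full protocol or analysis plan.
- **That the trial is underpowered.** A shortfall needs SD 6 to be the final-score SD, a test on change, and a low enough correlation. None of these is established, and the 75% figure sits at the adverse end of the cases shown.

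**Conclusion.** The point holds as a matter of efficiency and of fixing the primary analysis in advance. The stated test leaves its quantity undefined, makes the choice of method depend on the data, and does not adjust for a baseline score already collected.

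Adjustment is at least as powerful as the unadjusted test in every case computed. With SD 6 as the final-score SD and 119 per group, it raises power from about 90% for an unadjusted comparison of final scores to about 92.5% at r = 0.3 and 97% at r = 0.5.

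Loss below 90% with a change score is conditional. With equal SDs it occurs only if r is below 0.5. It shrinks with a smaller baseline SD and vanishes if SD 6 is the SD of change. The correlation and the baseline SD are assumptions, since the document gives neither. The 119 and 300 need no correction.

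**What to change.** 1. Name one primary analysis: the between-arm difference in month-12 BDI adjusted for baseline BDI, with its confidence interval. Either ANCOVA or a repeated-measures mixed model would serve. The mixed model would also use month-6 BDI and include all randomized patients with any follow-up score.
2. For BDI, remove the choice of test by normality and the post-hoc contrasts. Keep a rank test as a sensitivity analysis at most.
3. Define t0-tk, and state whether SD 6 refers to the final score or to the change.

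The cost is wording and minor programming. No new data and no change in sample size are needed. It should be settled before outcome data are seen.
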